## Methods/Design

### Trial design

The Teemo study is designed as a single-center, randomized controlled, investigator-blinded superiority trial with two parallel groups and a primary endpoint of maternal sensitivity and child responsiveness after 9 months of intervention. Randomization will be performed as block randomization with a 1:1 allocation. The trial is located at the Department of Child and Adolescent Psychiatry, University Hospital RWTH Aachen.

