### Intervention: STEEP-b

The intervention (STEEP-b) is an adaptation of the STEEP program [35], which aims to enhance sensitive care using video-feedback to guide parents to recognize their children’s signals, take their children’s perspective and understand their children’s needs. STEEP-b was designed to be relatively brief, completed in 12 to 18 sessions, and started when the children are between 3 and 6 months of age (as a detailed meta-analysis could demonstrate [25], interventions with a small to moderate number of sessions and those with an older infant are more effective than longer interventions and those with very young infants). Adolescent mothers are visited at home every 2 to 3 weeks by the same adviser for 9 months. Furthermore, an optional group meeting is offered every second month that mothers can attend. The exact number of sessions will depend on clinical appropriateness in the 9-month window. The original STEEP program is not manualized; however, as treatment manualization is considered an important factor in treatment integrity and effectiveness [25, 36], STEEP-b has been modularized with every session focusing on one of four obligatory modules. The four modules emphasize the following elements: child development, maternal sensitivity, frightening and intrusive behaviors and sensitive discipline. Every module should be worked on twice, with the order depending on clinical appropriateness. A promising tool to increase sensitive parenting is video-feedback [25]. A study in adolescent mothers demonstrated positive maternal behaviors and improved affective scores after video feedback of mother-infant interaction, but not in a control group [37]. Therefore, video-feedback of free interaction situations and structured interaction situations will be used to work on the intervention topics. In addition, if the baseline assessment reveals any psychiatric diseases in the mother (for example, depression or PTSD), arrangements will be made for individual psychiatric treatment to be offered by a qualified clinical psychologist or psychiatrist within 4 weeks after the diagnostic assessments. The intervention is discontinued at the participant’s request or if interventions are no longer possible due to the separation of the mother and child (>3 months) or any other serious harm (severe illnesses of either mother or child, death of participants) preventing study participation. Whenever possible, study participants are retained in the trial to enable follow-up data collection and to prevent missing data. Participants who are assigned to the TAU arm are not allowed to receive any intervention using video-feedback.

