### Sample size calculation and statistical analysis

Based on a large meta-analysis [25], we expect at least moderate effect sizes for maternal sensitivity and child responsiveness (Cohen’s d = 0.5). Assuming a small correlation between baseline and follow-up T2 of 0.25, the standardized effect of d = 0.5 can be detected with a power of 80 % for a two-sided significance level of 5 % with a total sample size of 120 mother-child dyads. Based on Suess *et al*. [28], we expect drop-out rates of approximately 30 % during the longitudinal study; therefore, 180 individuals will be randomized in total to obtain at least 120 evaluable mother-infant dyads. In addition, we expect that approximately 20 % of the screened mothers cannot be included in the study due to violation of the inclusion/exclusion criteria. Hence, 220 to 230 mothers will be assessed for eligibility. If the planned sample size cannot be achieved within the time frame of funding, the Trial Steering Committee and the responsible biometrician of the Data management Team can decide to terminate the trial before the intended sample size is achieved.

All main analyses will be carried out at the end of the last follow up assessment and will be based on the intention to treat principle. Two primary hypotheses, one on the maternal outcome and the other on the child’s outcome, will be tested:H_0_: The change from baseline to the 9-month follow-up T2 in maternal sensitivity/child’s responsiveness is equal in the intervention and the control group.H_1_: The change from baseline to the 9-month follow-up T2 in maternal sensitivity/child’s responsiveness is different in the intervention and the control group.

An analysis of covariance will be used for primary analyses using the EAS Score at the follow-up T2 as the dependent variable and the baseline value and group allocation as covariates. All other analyses will be performed descriptively. Means and standard deviations or absolute and relative frequencies will be reported according to the underlying scale level. A detailed statistical analytical plan will be written by the trial statistician and signed off by the principle investigator.

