### Methods against bias

Eligibility assessment, obtaining informed consent, and enrolling the patient in the trials is performed at the trial site by one of the investigators.

Subjects are randomly assigned to either group using a web-based randomization system (http://www.randomizer.at) in a ratio 1:1. Data entry for randomization is done by the STEEP-b trainer and takes place after all baseline measurements to ensure allocation concealment. The randomization tool is supervised by the Institute of Medical Biometry and Informatics of the University of Heidelberg, Germany. Block randomization using fixed block lengths is used, stratified for mother’s age (<18 years or >18 years).

To ensure that all trainers implement STEEP-b in a very comparable way, all therapists are trained before the beginning of the study, and application of the modularized sessions is strictly monitored. In addition, therapists are supervised by an experienced STEEP therapist ([name], STEEP training director in Germany). For the assessments of adherence and competence, sessions will be audiotaped. We will obtain independent judgments on the quality of therapy using a random selection of therapy tapes. Patients will also be asked to assess the intervention and the therapist’s empathy post-intervention.

Data quality is continuously monitored by the Data Management Team (Institute of Medical Biometry and Informatics (IMBI), University of Heidelberg and the Coordination Centre for Clinical Trials Heidelberg (KKS)). Data will be entered electronically at the IMBI. Range checks for data values are done to promote data quality. The original study forms will be kept at the trial site. Participants’ files are stored in locked cabinets and access to the study data will be restricted. Data will be collected, processed and stored according to the data protection laws. The principal investigators will be given access to the cleaned data sets.

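### The primary ANCOVA omits mother's age, the factor by which randomisation is stratified; if age is prognostic the test is conservative and loses a little power

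*Protocol article*

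**What the plan says.** All references are to the protocol article.

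- **Sample size calculation and statistical analysis.** There are two primary hypotheses, one for maternal sensitivity and one for child responsiveness. Both are tested by an ANCOVA "using the EAS Score at the follow-up T2 as the dependent variable and the baseline value and group allocation as covariates". No further term is listed. A detailed SAP is announced but not shown.
- **Methods against bias.** "Block randomization using fixed block lengths is used, stratified for mother’s age (<18 years or >18 years". Age is the only stratification factor named.
- **Trial design.** "Randomization will be performed as block randomization with a 1:1 allocation".
- **Sample size inputs.** The effect size is given as "we expect at least moderate effect sizes for maternal sensitivity and child responsiveness (Cohen’s d = 0.5". For the gain from baseline adjustment, the article writes "Assuming a small correlation between baseline and follow-up T2 of 0.25". The target is then "power of 80 % for a two-sided significance level of 5 % with a total sample size of 120 mother-child dyads".

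Nowhere does the article say that age will enter the primary model.

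**The concern.** Stratified blocks force the two arms to be nearly equal in age mix. The true sampling variance of the treatment difference therefore no longer contains the part due to age. An ANCOVA without age does not know this. It leaves any age variance in the residual and computes the standard error as if age had been left to chance. The interval is then wider than it should be, the type I error falls below 5 %, and some power is given away.

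The covariate list is explicit, so this is a choice the article makes and not a detail left open. An SAP that follows the article inherits the mismatch, and one that adds age departs from the published primary model.

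The stratum definition adds a smaller problem. Under 18 and over 18 do not cover a mother aged exactly 18, who is eligible under Table 1. If age is counted in completed years, that is a whole year of eligible mothers.

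**Working it through.** **1. The plan's own figure.** Inputs from the article: d = 0.5, correlation 0.25, power 80 %, two-sided 5 %, 1:1 allocation. The residual variance after baseline adjustment is 1 − 0.25² = 0.9375.

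n per arm = 2 × (1.96 + 0.842)² × 0.9375 / 0.5² = 58.9, so 59 per arm and 118 in total. With the t distribution, 60 per arm gives 80.1 % power. The stated 120 is therefore reproduced by a model with baseline and group only.

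**2. Assumptions that the article does not supply.** 25 % of mothers are under 18 and blocks have length 4. The age effect on the T2 score, given baseline, is 0, 0.5 or 0.8 SD and comes on top of the residual variance of 0.9375.

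**3. Formulas, with 60 per arm.**
- Age variance = b² × 0.25 × 0.75, where b is the age effect.
- SE that the model without age reports = √[(0.9375 + age variance) × 2/60].
- SE with age in the model = √(0.9375 × 2/60) = 0.177. Because the blocks balance age, this is also close to the true SE of the estimate without age.
- r = ratio of the first SE to the second.
- Type I error without age = 2Φ(−1.96 r).
- Power without age = Φ(0.5/0.177 − 1.96 r). Power with age uses r = 1.

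| Age effect | Age variance | Model SE without / with age | r | Type I error without age | Power without / with age |
|---|---|---|---|---|---|
| 0 | 0 | 0.177 / 0.177 | 1.000 | 5.0 % | 81 % / 81 % |
| 0.5 SD | 0.047 | 0.181 / 0.177 | 1.025 | 4.5 % | 79 % / 81 % |
| 0.8 SD | 0.120 | 0.188 / 0.177 | 1.062 | 3.7 % | 77 % / 81 % |

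**4. Check by simulation.** In 20,000 simulated trials per setting, with stratified blocks of 4 and t tests, power without / with age was 80.1 % / 80.1 % at 0, 78.3 % / 79.7 % at 0.5 SD and 75.7 % / 79.6 % at 0.8 SD. Type I error without age at 0.8 SD was 3.9 %. The estimates centred on the true effect under both models. At 0.8 SD their empirical SD was about 0.177 for both models under no treatment effect, while the model without age reported 0.188. The normal formulas run about one point high. The loss is one to two points at 0.5 SD and three to four at 0.8 SD.

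**5. The other way to set it up.** If the planned SD already includes the age variance, the total residual variance stays at 0.9375 and age explains a share R² of it. With 30 % under 18, blocks of 4 and 8,000 simulated trials per setting:

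| R² | Type I error without / with age | Power without / with age |
|---|---|---|
| 0.01 | 0.049 / 0.050 | 0.793 / 0.793 |
| 0.05 | 0.046 / 0.051 | 0.798 / 0.814 |
| 0.10 | 0.041 / 0.051 | 0.803 / 0.830 |
| 0.20 | 0.027 / 0.050 | 0.818 / 0.874 |

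The two scales connect. In step 3, 0.5 SD is R² = 0.047/0.984 = 0.048, and 0.8 SD is R² = 0.120/1.0575 = 0.113. On this reading the plan still reaches about 80 %, and what it forgoes is a gain.

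**The case against.** The strongest reply is that the effect may be nil. The article gives no age effect on Emotional Availability among mothers of 21 or younger. Its Background contrasts adolescent with adult mothers, which says little about those under 18 against those a few years older. At R² = 0.01 nothing visible changes, and 0.8 SD between neighbouring age groups is a large assumption. The share under 18 and the block length are assumed too. All of this stands. It limits the size of the point but does not remove the mismatch, and the remedy costs almost nothing even if age is irrelevant.

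A second reply is that an SAP is still to come. That would answer a missing detail, but here the covariates are listed.

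A third is that the age wording is probably a slip. Allocation runs through a supervised web system, and nothing suggests that 18-year-olds could not be randomised. That is fair, and it is why the boundary should be read from the system and not guessed.

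Two stronger readings are tempting. A reader might infer that the standard errors are wrong in a way that produces false positives. Omitting the stratum does the opposite, and only if age is prognostic. A reader might also infer, from "Adolescent mothers are visited at home every 2 to 3 weeks by the same adviser for 9 months", that dyads sharing a trainer make the standard error too small. The nesting in the STEEP-b arm is real. However, the article gives neither the number of trainers nor an intraclass correlation, and it describes common training, monitored sessions and supervision. Any size for that effect would be assumption alone, and a sensitivity analysis for it is ordinary SAP content.

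**Conclusion.** The point holds in a limited form. The stated primary model leaves out the one factor on which randomisation is stratified. The treatment estimate is not biased and the false-positive rate does not rise. If age is prognostic, the model SE is too large and the test is conservative. Under the assumptions in step 2 of the working, power is about 79 % against 81 % for an age effect of 0.5 SD. For 0.8 SD it is about 77 % against 80 %, with a type I error near 3.7 %. These figures move by about a point with the method of calculation. If age is not prognostic there is no loss. The sample size of 120 is correct on its own inputs.

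The mismatch and the gap at age 18 can be read directly from the text. The magnitudes depend on the assumed age effect, share under 18 and block length. The correction is worth making because it is nearly free, not because the trial's conclusion is in danger.

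**What to change.** State the primary model, for each of the two outcomes, as: T2 EA score = group + baseline EA score + age stratum. Take the stratum as it is implemented in the randomisation system, because recruitment has been running since October 2012 and the strata are already in use. Correct the description in Methods against bias so that mothers aged exactly 18 fall in the stratum actually used, and state the date at which age is taken. Carry the same wording into the SAP.

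The cost is one covariate, hence one degree of freedom out of 117, and one corrected sentence. With no age effect, the simulated mean model SE was 0.177 with or without the stratum, so nothing is lost. Whether to add a partially nested sensitivity analysis for trainers can be left to the SAP.

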### Methods against bias

Eligibility assessment, obtaining informed consent, and enrolling the patient in the trials is performed at the trial site by one of the investigators.

Subjects are randomly assigned to either group using a web-based randomization system (http://www.randomizer.at) in a ratio 1:1. Data entry for randomization is done by the STEEP-b trainer and takes place after all baseline measurements to ensure allocation concealment. The randomization tool is supervised by the Institute of Medical Biometry and Informatics of the University of Heidelberg, Germany. Block randomization using fixed block lengths is used, stratified for mother’s age (<18 years or >18 years).

To ensure that all trainers implement STEEP-b in a very comparable way, all therapists are trained before the beginning of the study, and application of the modularized sessions is strictly monitored. In addition, therapists are supervised by an experienced STEEP therapist ([name], STEEP training director in Germany). For the assessments of adherence and competence, sessions will be audiotaped. We will obtain independent judgments on the quality of therapy using a random selection of therapy tapes. Patients will also be asked to assess the intervention and the therapist’s empathy post-intervention.

Data quality is continuously monitored by the Data Management Team (Institute of Medical Biometry and Informatics (IMBI), University of Heidelberg and the Coordination Centre for Clinical Trials Heidelberg (KKS)). Data will be entered electronically at the IMBI. Range checks for data values are done to promote data quality. The original study forms will be kept at the trial site. Participants’ files are stored in locked cabinets and access to the study data will be restricted. Data will be collected, processed and stored according to the data protection laws. The principal investigators will be given access to the cleaned data sets.

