**Fig. 1 Fig1:**
[figure not shown]
Study flow chart

Due to the nature of the intervention neither participants nor trainers can be blinded to allocation. Therefore, all follow-up assessments are done by research staff members that are blinded. If unblinding occurs, another assessor will be brought in to re-establish blindness. Participants will be paid 50€ for each assessment session, and travel expenses will be refunded.

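### Entering the randomisation after baseline does not by itself ensure concealment when an unblinded trainer makes the entry, block lengths are fixed and there is one centre

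*Protocol article*

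**What the plan says.** Four statements in the protocol article bear on this point.

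- Methods against bias, on who enters and when: "Data entry for randomization is done by the STEEP-b trainer and takes place after all baseline measurements to ensure allocation concealment".
- The same section, on the scheme: "Block randomization using fixed block lengths is used", within two strata defined by the mother's age. Allocation is 1:1 through a web-based system supervised by an external biometry institute.
- Measurement time points (text below Fig. 1), on blinding: "neither participants nor trainers can be blinded to allocation".
- Trial design describes a "single-center, randomized controlled, investigator-blinded superiority trial".

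Methods against bias also contains a safeguard: "Eligibility assessment, obtaining informed consent, and enrolling the patient in the trials is performed at the trial site by one of the investigators". Screening, consent and enrolment are thus assigned to a different role from the one that enters the randomisation.

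The article gives no block length and no rule on the order in which dyads are entered.

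**The concern.** Concealment has two parts. The allocation of the dyad in hand must be unknown until it is irrevocably entered, and the allocation of the next dyad must not be predictable from those already made. Entry after baseline serves the first part. The article presents it as sufficient, but it does nothing for the second.

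The person at the keyboard delivers the experimental arm and sees the result of each entry made. With one centre and a constant block length, the pattern in each age stratum can in principle be followed and the length inferred. Near the end of a block the next allocation is then known.

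At stake is comparability of the arms. If more cooperative mothers were steered to STEEP-b, the arms would differ at entry in a way that could resemble an effect on maternal sensitivity or child responsiveness. Blinded rating does not prevent this. Adjustment for the baseline score removes only the part that the score captures. Whether any trainer would have a preference is an assumption, since the article says nothing on it.

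**Working it through.** The article gives no figure for predictability, so there is none of its own to reproduce. Inputs from the article are 1:1 allocation, fixed block length, one centre, unblinded trainers and 180 randomised (Sample size calculation and statistical analysis). Assumed, because not stated: a block length of 4, 6 or 8, and an observer who knows the length, the stratum and all past allocations.

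**Step 1: allocations known with certainty.** In a 1:1 block of length 2m, once one arm has used its m places, every remaining place is determined. The expected number of determined places is 2m/(m+1) per block, a share of 1/(m+1).

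**Step 2: best-guess accuracy.** The observer guesses the arm with more places left, and a tie counts one half. Expected correct guesses per block are m + 2^(2m−1)/C(2m, m) − 1/2.

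| Length | Certain | Of 180 | Correct guesses per block | Accuracy |
|---|---|---|---|---|
| 4 | 1/3 = 33.3 % | 60 | 2 + 8/6 − 0.5 = 2.833 | 70.8 % |
| 6 | 1/4 = 25.0 % | 45 | 3 + 32/20 − 0.5 = 4.100 | 68.3 % |
| 8 | 1/5 = 20.0 % | 36 | 4 + 128/70 − 0.5 = 5.329 | 66.6 % |

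Chance accuracy is 50 %. The counts out of 180 treat all blocks as complete. Exact enumeration of all blocks gives the same shares and accuracies.

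**Step 3: what the trainer could do with this.** The places left in a block are exchangeable. Reordering mothers who will all be entered in that block therefore changes nobody's chances. Order matters when waiting mothers of the same stratum straddle a block end, or when one is held back past it. For example, with length 4, after two TAU and one STEEP-b the last place is STEEP-b for certain, while the first place of the next block is 50:50. With two mothers waiting, the trainer could choose who takes the known place. The shares in Step 1 therefore measure predictability, not the proportion of allocations that could be steered. The article gives no recruitment rate or queue length from which to estimate the latter.

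**Step 4: effect of varying the block length.** Simulation (300 runs of 180 allocations) assumed an observer who knows the set of lengths in use but not the length of each block.

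| Lengths in use | Certain | Accuracy |
|---|---|---|
| 4 and 6 | 5.7 % | 69.2 % |
| 4, 6 and 8 | 2.4 % | 68.0 % |

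Most certain predictions disappear. Best-guess accuracy hardly moves against 70.8 % (fixed 4) and 68.3 % (fixed 6).

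**Step 5: what baseline adjustment can absorb.** The planned correlation between baseline and T2 is 0.25, so the baseline score explains 0.25² = 0.0625, about 6 %, of the outcome variance. Selection on traits such as motivation would be largely unadjusted.

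**The case against.** The strongest reply is that investigators, not trainers, do screening, consent and enrolment. By the time a trainer enters a dyad, the mother has consented and completed T1, and analysis is by intention to treat. The trainer cannot decide who is in the trial. This stands, and it confines the direct route to the order of entry described in Step 3.

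A reader might infer more: that one trainer sees the whole sequence, and that the next allocation is known before a mother is approached. The article does not support either reading. It speaks of several trainers and does not say whether each sees the others' results. Influence on who is approached would need information to pass from trainers to the enrolling investigators, which the text neither shows nor excludes.

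It is also fair to say that the block length may be withheld from the site, and that a condensed article may leave this to the full protocol. The missing length is therefore not itself the criticism, and the percentages are conditional on it being known or inferred. Withholding a fixed length is weak protection, however, when those who see the results work at one site.

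The web tool hides the list, and assessors and video raters are blinded. Those are real protections against looking up an allocation and against biased rating. Neither addresses prediction from past allocations.

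**Conclusion.** The point holds as an avoidable risk and an unsupported assurance. The timing of entry, which the article gives as the means of ensuring concealment, does not prevent prediction of upcoming allocations under the stated combination of unblinded trainer, single centre and fixed blocks.

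If the length is known or inferred and past allocations are visible, one third to one fifth of allocations would be certain in advance for assumed lengths of 4 to 8. These figures describe predictability. They do not translate into a bias in maternal sensitivity or child responsiveness, and nothing in the article allows that step. A reader might conclude that concealment failed, but the article contains no evidence of that. Confidence is moderate, because the block length, the trainers' view of each other's entries and the order of entry are not described.

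**What to change.** The article reports that recruitment is still open, so the change can apply to all remaining dyads.

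1. Set the web tool to randomly varying block lengths and do not disclose them to the site. This removes most certain predictions but only slightly affects best-guess accuracy, so it is not enough alone.
2. Have existing staff who neither deliver STEEP-b, enrol nor assess outcomes make each entry, strictly in order of T1 completion, and tell the trainer only the result. This closes the order-of-entry route. The institute that supervises the tool is one candidate, although the article does not show whether it has the capacity.
3. Reword the assurance: entry after baseline protects the baseline data, while concealment rests on items 1 and 2.
4. Report baseline balance before and after the change.

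The cost is a tool setting, a short hand-over between T1 completion and allocation, and a formal amendment with ethics approval, which the article requires for any modification. Balance within strata becomes slightly looser: the difference between arms within a stratum can reach half the longest block, for example 4 with a block of 8 against 2 with a block of 4. No extra visits or participants are needed.
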